### Data collection and management

Data were collected using a secure electronic case report form (eCRF) system built on a validated platform compliant with regulatory standards. All study personnel were trained in Good Clinical Practice and received specific instruction on eCRF completion prior to study initiation. Data entry was performed in real-time or shortly after each study visit by trained research coordinators. Built-in range checks, logical validations, and mandatory field requirements were implemented to minimize entry errors at the point of data capture.

Discrepancies and missing data triggered automated queries, which were resolved by site staff with reference to source documents. All data modifications were tracked via an audit trail that recorded the user, date, time, original value, and revised value. Access to the eCRF was role-based, with modification rights restricted to designated personnel; investigators had read-only access to their own site data after database lock.

Data quality was monitored through a multi-layered approach. Monthly central audits assessed completeness and protocol compliance. Source data verification was conducted on 10% of randomly selected participants, with a pre-specified acceptability threshold of >95% consistency between eCRF and source documents. Standard operating procedures governed data cleaning, query resolution, coding of adverse events (if applicable), and database lock. The research quality and data quality monitoring committee will review our raw data regularly.

Electronic data were stored on secure servers with restricted access, daily backups, and encryption both at rest and in transit. Physical and digital confidentiality measures were enforced in accordance with institutional ethics committee requirements and national data protection regulations. All study data will be retained for at least 10 years after study completion, after which they will be anonymized or destroyed per regulatory guidelines.

### Vaginal microbiome sample collection and storage

Participants were instructed to abstain from sexual intercourse, vaginal medication, and douching for 48 h prior to sampling. For patients who are menstruating at baseline, sampling was scheduled 3–7 days after the cessation of menstruation to minimize interference from the menstrual cycle. At follow-up visits, most participants will be amenorrheic due to OFS; however, if a participant reports any vaginal bleeding, sampling will be rescheduled until bleeding has ceased for at least 3 days. During the procedure, patients were placed in the lithotomy position. A sterile vaginal speculum was used to fully expose the cervix. A sterile cotton swab was rotated in the posterior vaginal fornix for 10 s to collect the specimen, since this anatomical reservoir pools cervicovaginal secretions, providing a highly representative and stable sample of the vaginal microbiome and mucosal microenvironment. The swab was immediately placed into a sterile tube containing DNA/RNA Shield™ preservative, temporarily stored at 4 °C, and transferred to a – 80 °C ultra-low temperature freezer within 4 h for long-term storage.

### Microbial DNA extraction and 16S rRNA gene sequencing

Total microbial DNA was extracted from vaginal swab samples using a bacterial DNA extraction kit according to the manufacturer’s instructions. DNA purity and concentration were assessed using a NanoDrop One spectrophotometer. Using the qualified DNA as a template, the V3–V4 region of the 16S rRNA gene was amplified via PCR using universal primers 338F (5′-ACTCCTACGGGAGGCAGCA-3′) and 806R (5′-GTACTACVGGGTWTCTAAT-3′). A unique barcode was attached to the reverse primer for each sample.

PCR reactions were performed in a 50 μL volume containing 25 μL of 2 × Premix Taq, 2 μL each of 10 μM forward and reverse primers, 50 ng of DNA template, and nuclease-free water. The thermal cycling profile consisted of an initial denaturation at 95 °C for 3 min, followed by 30 cycles of denaturation at 95 °C for 30 s, annealing at 53 °C for 30 s, and extension at 72 °C for 30 s, with a final extension at 72 °C for 5 min. PCR product concentration was determined using NanoDrop. Samples with different barcodes were mixed in equimolar ratios. The mixture was further purified using agarose gel electrophoresis and analyzed with GeneTools software (v4.03.05.0; SynGene, United States); samples showing a bright main band at approximately 470 bp were selected for subsequent steps. Sequencing libraries were generated using the ALFA-SEQ DNA Library Prep Kit (DL1010). Library quality was assessed using a Qubit 2.0 Fluorometer and an Agilent 2,100 Bioanalyzer system. Paired-end 250 bp (PE250) sequencing was performed on the Illumina NovaSeq 6,000 platform.

### Sequence processing and amplicon sequence variant (ASV) analysis

Raw reads were processed using Fastp (v0.14.1) and Cutadapt to remove adapters, primers, short reads (<100 bp), and low-quality reads (defined as reads containing >10% unknown bases or >20% bases with a *Q*-value <20). Denoising and Amplicon Sequence Variant (ASV) inference were performed using the DADA2 pipeline (via QIIME 2). Briefly, forward and reverse reads were trimmed, filtered, denoised, merged, and chimeric sequences were removed using the DADA2 plugin, which is highly recommended for vaginal microbiome research to accurately differentiate closely related Lactobacillus species. ASVs were then clustered at 100% sequence identity. Taxonomic assignment of ASVs was performed using the q2-feature-classifier plugin with the SILVA database (v138). Representative sequences for each ASV were aligned against the SILVA database (v138) for taxonomic annotation.

### Diversity analysis and community structure assessment

Alpha diversity was evaluated by calculating the Shannon Index and Simpson index based on the ASV abundance matrix to assess species richness and evenness within samples. Differences between groups were analyzed using the Kruskal-Wallis test. Beta diversity was assessed by calculating Bray-Curtis distances and weighted/unweighted UniFrac distances between samples and visualized using Principal Coordinates Analysis (PCoA). Permutational multivariate analysis of variance (PERMANOVA), implemented via the adonis function in the R vegan package, was used to quantitatively evaluate the variation in microbial community structure explained by clinical grouping. To ensure robustness, ASV-level analyses were compared with genus-level aggregated data as a sensitivity analysis.

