**Methods:**

This single-center prospective cohort at Women’s Hospital, Zhejiang University School of Medicine, will enroll 110 premenopausal women (18–45 years) with hormone receptor-positive breast cancer, allocated to OFS + AI or OFS + TAM based on clinical regimens. Vaginal swabs collected at baseline and 1, 3, 6, 12 months undergo 16S rRNA sequencing (V3-V4 region) with DADA2-based ASV analysis via QIIME 2 for species-level resolution. Assessments include Vaginal Health Index (VHI), GSM symptoms (VAS for dryness, dyspareunia, burning), s, and urinary symptoms (ICIQ-SF). Primary outcomes: microbiome diversity (Simpson index) and Lactobacillus abundance. Secondary: VHI, VAS, urinary scores. Analyses use repeated measures ANOVA and generalized estimating equations; sample size accounts for medium effect (*d* = 0.8) and 10% attrition. Ethically approved and registered in Chinese Clinical Trial Registry.

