### Sample size

This study utilized a sample size calculation formula designed for comparing means between two independent groups. Our preliminary pilot-study data indicated a Simpson index of 0.8 in the OFS + AI group and 0.1 in the OFS + TAM group, with an effect size of *δ* = 0.7. Based on the literature-reported standard deviation of vaginal microbiota diversity (*σ* = 0.2), the effect size was calculated as d = δ/σ. The significance level was set at *α* = 0.05, with a statistical power of 1 - *β* = 0.8. The calculations suggested that 25 participants per group were necessary to detect a moderate effect size difference. Based on an annual cohort of 500 breast cancer patients, 20–30% (100–150 patients per year) are younger than 50 years. Over our planned 2-year recruitment period, we expect 200–300 eligible patients. Assuming a conservative recruitment rate of 40–50%, this allows us to successfully meet our target sample size of 110 participants (55 participants per group).

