### Statistical analysis

This study utilized both the full analysis set (FAS) and the per-protocol set (PPS) for statistical evaluation. The FAS will include all enrolled participants who receive at least one dose of treatment and provide baseline data, analyzed according to their assigned group to minimize selection bias. The PPS will comprise participants who complete the study per protocol, excluding those with major violations such as non-adherence to treatment or loss to follow-up exceeding predefined thresholds. All tests will be two-sided, with a significance level of *α* = 0.05. Descriptive statistics will summarize continuous variables as mean ± standard deviation for normally distributed data or as median (interquartile range) for skewed distributions. Categorical variables will be presented as frequencies and percentages.

Given the observational nature of this cohort study, baseline imbalances between groups will be assessed using standardized mean differences. If substantial imbalances are detected (standardized mean difference >0.1 for key covariates), propensity score matching will be applied to create balanced subgroups for comparative analyses, with propensity scores estimated via logistic regression incorporating variables such as age, BMI, tumor stage, hormone receptor status, and chemotherapy history.

Between-group comparisons will use independent samples t-tests or Mann–Whitney U tests for continuous variables, depending on data distribution and variance homogeneity. Chi-square or Fisher’s exact tests will be applied for categorical variables.

For longitudinal analyses, we plan to use linear mixed-effects models (LMM) for continuous clinical outcomes (e.g., GSM symptom scores) and generalized linear mixed models (GLMM) for microbiome features (e.g., relative abundance of key taxa). Therapy group, time point, and their interaction will be included as fixed effects to evaluate whether temporal trajectories differ by treatment type. Repeated measures ANOVA (RM-ANOVA) will be retained only as a secondary sensitivity analysis for complete-case datasets. If the proportion of missing data for a given outcome exceeds 10%, multiple imputation by chained equations (MICE) will be performed under the missing-at-random (MAR) assumption, with 20 imputed datasets and pooled estimates using Rubin’s rules.

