The potential impacts and translational value of this study protocol are evident in multiple clinical and scientific areas. First, by integrating 16S rRNA sequencing data with clinical parameters (such as VHI scores, GSM symptom VAS, and FSFI assessments), the protocol design supports the development of a microbiota-GSM prediction model for early risk stratification and personalized preventive interventions; for instance, longitudinal microbiota sampling (at baseline and 1, 3, 6, 12 months) can identify high-risk patients and guide targeted probiotic supplementation, thereby reducing treatment discontinuation rates from 30 to 15% (25). Second, the protocol provides microbiological evidence to optimize endocrine therapy selection, particularly for patients at elevated GSM risk, by comparing microbial dynamic changes (e.g., Lactobacillus relative abundance and diversity metrics) between the OFS + AI and OFS + TAM groups, facilitating personalized clinical decision-making. Third, the protocol’s standardized assessment framework (including repeated measures analysis of variance and generalized estimating equations) will establish vaginal microecology evaluation standards for Chinese premenopausal breast cancer patients, addressing the data gap in Asian populations and contributing longitudinal evidence to international guideline development.

This study boasts several strengths, primarily its prospective cohort design, which effectively captures the real-time effects of endocrine therapy on the dynamics of the vaginal microbiome. Additionally, with standardized assessment tools and a multidisciplinary team approach, we ensure the reliability and comprehensiveness of the data. The sample size and follow-up timeframes have also been carefully considered to adequately reflect changes in the vaginal microbiome and their associations with genitourinary syndrome of menopause (GSM) symptoms. This comprehensive approach provides valuable longitudinal evidence for both domestic and international guideline development.

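### The analysis of the primary Simpson index is stated inconsistently, and the test attached to it by name cannot carry the planned confounding control

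*Protocol article*

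**What the plan says.** The primary outcomes are microbial diversity (the Simpson index, per the abstract) and the relative abundance of Lactobacillus. Swabs are taken at baseline and at 1, 3, 6 and 12 months.

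Statements on how these outcomes are analysed:

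- **Diversity analysis and community structure assessment**, directly after introducing the Shannon and Simpson indices: "Differences between groups were analyzed using the Kruskal-Wallis test". For beta diversity it names PERMANOVA, "implemented via the adonis function in the R vegan package".
- **Abstract, Methods**, directly after listing the outcomes: "Analyses use repeated measures ANOVA and generalized estimating equations".
- **Discussion**, describing the assessment framework: "including repeated measures analysis of variance and generalized estimating equations".
- **Statistical analysis**: t-tests or Mann-Whitney tests for between-group comparisons of continuous variables; LMM for continuous clinical outcomes; and "generalized linear mixed models (GLMM) for microbiome features (e.g., relative abundance of key taxa"), with regimen, time and their interaction as fixed effects. It then says "Repeated measures ANOVA (RM-ANOVA) will be retained only as a secondary sensitivity analysis for complete-case datasets". GEE does not appear in this section.

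Statements on confounding control:

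- **Cohort classification**: inverse probability of treatment weighting (IPTW) is the primary approach.
- **Statistical analysis**: propensity score matching is applied if a key covariate has a standardized mean difference above 0.1.
- **Statistical analysis**, multivariable part: covariate-adjusted regression and mixed models, with stepwise selection, for the effect of regimen on microbiota changes.

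**The concern.** Repeated measures ANOVA cannot be both the headline method (abstract, Discussion) and a complete-case sensitivity analysis only (Statistical analysis). GEE cannot be a main method in two places and absent from the section that defines the methods. The Simpson index therefore has several candidate analyses, some adjusted and some not, and none is designated primary. That leaves room to choose after the data are seen.

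The choice matters here. Under Cohort classification, OFS + AI is preferred for women at high risk of recurrence, and chemotherapy history is itself named as a potential confounder. A standard Kruskal-Wallis test takes no weights, covariates or baseline value. The test attached to the primary diversity measure therefore does not implement the confounding strategy that the protocol calls primary.

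**Working it through.** The protocol gives no error rate or effect figure for this point, so there is nothing of its own to reproduce. The check sets the statements side by side and then sizes what is at stake.

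**1. What each section offers for the Simpson index**

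| Section | Method | Weights or covariates | Repeated visits |
|---|---|---|---|
| Diversity analysis | Kruskal-Wallis | none stated | no visit stated |
| Abstract, Discussion | RM-ANOVA and GEE | none stated | yes |
| Statistical analysis | t-test or Mann-Whitney | none stated | no |
| Statistical analysis | GLMM for microbiome features | adjustment in the multivariable part | yes, regimen x time |
| Statistical analysis | RM-ANOVA | none stated | sensitivity analysis only |

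No section ranks Kruskal-Wallis against GLMM or GEE for alpha diversity.

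**2. Confounding at a single visit**

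Inputs from the protocol: two-sided 0.05 ("All tests will be two-sided, with a significance level of *α* = 0.05"), 55 women per group, 10% attrition. This leaves 55 x 0.9 = 49.5, taken as 50 per group. Assumed, not in the protocol: a binary confounder with a prevalence difference of 20 to 50 points between regimens and an effect of 0.5 to 0.8 SD on the outcome. There is no true regimen effect.

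Formulas: bias = prevalence difference x effect; SE = sqrt(2/50) = 0.20 SD; type I error = P(|Z + bias/SE| > 1.96).

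| Difference | Effect | Bias (SD) | Bias/SE | Type I error |
|---|---|---|---|---|
| 20 points | 0.5 SD | 0.10 | 0.50 | 0.079 |
| 35 points | 0.5 SD | 0.175 | 0.875 | 0.141 |
| 50 points | 0.5 SD | 0.25 | 1.25 | 0.240 |
| 35 points | 0.8 SD | 0.28 | 1.40 | 0.288 |
| 50 points | 0.8 SD | 0.40 | 2.00 | 0.516 |

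The range is about 8% to 52%. Simulated Kruskal-Wallis tests at 55 per group (5,000 runs each) agree at the two ends: 0.077 for prevalences 60% v 40% and 0.5 SD, and 0.494 for 80% v 30% and 0.8 SD.

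**3. Pooling all five visits (conditional)**

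The protocol does not say that visits are pooled. If they were, the design effect would be 1 + (5 - 1) x ICC, and the type I error would be 2 x (1 - Φ(1.96/sqrt(design effect))). The ICC is assumed.

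| ICC | Design effect | Formula | Simulation, 3,000 runs, 55 v 55 |
|---|---|---|---|
| 0.3 | 2.2 | 0.186 | 0.188 |
| 0.5 | 3.0 | 0.258 | 0.265 |
| 0.7 | 3.8 | 0.315 | 0.320 |

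A second simulation of 2,000 runs gave 0.18, 0.26 and 0.30. The range is about 18% to 32%, against a nominal 5%.

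**The case against.** The strongest reply is that the plan does deal with confounding and repeated sampling. Weighting, matching, covariate adjustment, chemotherapy subgroups and regimen-by-time mixed models are all there. Relative abundance is only an example of a microbiome feature, so GLMM may well be meant for the Simpson index too. A rank test on matched women would not be unadjusted. All of this stands. A reader might infer that the plan ignores confounding and within-woman correlation, or that Kruskal-Wallis is its definitive analysis of alpha diversity. The text supports neither.

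A reader might also infer that the five swabs are pooled as independent samples, or that PERMANOVA permutes them freely across visits. The article says neither, so the pooled error rates are conditional and no error rate is put on PERMANOVA. Nor does the article say that women on OFS + AI have had more chemotherapy, only that they are at higher recurrence risk. The confounder sizes are assumptions.

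Finally, a journal article may leave model details to a full protocol or SAP. That would excuse silence. It does not excuse sections that give the same method opposite roles, or three unreconciled methods of confounding control.

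**Conclusion.** The point holds as an inconsistency that leaves the primary analysis of the Simpson index unfixed. It rests on the text alone: Kruskal-Wallis in one section, RM-ANOVA and GEE in two, GLMM with RM-ANOVA demoted and GEE absent in another, and three confounding methods of which one is called primary.

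That Kruskal-Wallis cannot carry the weights or covariates is a property of the test. In a cohort allocated by clinical risk, using it as the regimen comparison would give a confounded contrast, even at a single visit. How badly confounded is not known from the protocol. The 8% to 52% and 18% to 32% ranges only illustrate the stakes under stated assumptions, and are not error rates of the plan. The inconsistency should be resolved before outcome data are analysed.

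**What to change.** Name one primary analysis per primary outcome, and state it identically in the abstract, Cohort classification, Diversity analysis, Statistical analysis and Discussion:

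- Apply the longitudinal model of the Statistical analysis section (regimen, visit, regimen x visit) explicitly to the Simpson index and to Lactobacillus relative abundance. Use the 1, 3, 6 and 12-month values as outcomes, the participant's baseline value as a covariate, and participant-clustered standard errors. A linear model for the Simpson index and a logit-link model for the Lactobacillus proportion would serve.
- Keep IPTW as the single primary confounding method. Make matching and covariate adjustment sensitivity analyses.
- State one primary contrast in advance. The 12-month regimen difference is one option; the choice is the investigators'.
- Label Kruskal-Wallis as descriptive.
- Run PERMANOVA per visit, or permute whole women rather than samples.
- Replace the RM-ANOVA and GEE wording in the abstract and Discussion with the chosen model.

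The cost is wording and analysis code. No new data are needed. Weighting will inflate the variance somewhat.

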In summary, while recent pioneering studies have begun to explore the longitudinal changes in the vaginal microecology of breast cancer patients undergoing endocrine therapy (23, 24), key knowledge gaps persist regarding the comparative effects of OFS + AI versus OFS + TAM on vaginal microbiota dynamics and the dose–response relationships between microbiome shifts and GSM severity. Therefore, this prospective cohort study aims to further contribute to this growing body of evidence by evaluating the effect of endocrine therapy on vaginal microbiome and GSM. This prospective cohort study aims to: (1) characterize the temporal changes in vaginal microbiome *α*-diversity (Simpson index), *β*-diversity, and relative abundance of predominant taxa (particularly Lactobacillus species) over 12 months in patients receiving endocrine therapy with ovarian function suppression; (2) compare the impact of two common regimens-ovarian function suppression combined with aromatase inhibitors (OFS + AI) versus ovarian function suppression combined with tamoxifen (OFS + TAM)-on vaginal microbiome composition; and (3) explore the associations between these microbiome changes and the severity of GSM symptoms, including potential dose–response relationships, as assessed by validated clinical measures (Vaginal Health Index, visual analog scales, and urinary symptom scores).

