### Primary outcome

This study identified vaginal microbial diversity and the relative abundance of Lactobacillus as the primary outcome measures. High-throughput sequencing of the 16S rRNA V3-V4 region was utilized, and bioinformatics analysis was conducted using the DADA2 pipeline via QIIME 2 to generate ASVs, enabling single-nucleotide resolution for quantitative assessment of alterations in vaginal microecological diversity. Species-level identification, particularly for Lactobacillus species, will be performed based on ASV taxonomic assignment. Simultaneously, the relative abundance of the Lactobacillus genus within the total bacterial community was analyzed to evaluate vaginal microecological homeostasis. Measurement time points were established at baseline, and at 1 month, 3 months, 6 months, and 12 months post-treatment, thereby creating a comprehensive longitudinal observation trajectory.

The collection of vaginal microbial samples followed a strictly standardized procedure: participants were instructed to abstain from sexual intercourse, vaginal medications, and douching for 48 h prior to sampling. Additionally, individuals who were menstruating were scheduled for sampling within a 3- to 7-day window following the cessation of menstruation to minimize interference from the menstrual cycle. During the sampling process, participants were positioned in the lithotomy position, and the cervix was fully exposed using a sterile vaginal speculum. A sterile cotton swab was rotated in the posterior vaginal fornix for a duration of 10 s, subsequently placed into a sterile tube containing DNA/RNA Shield preservative, temporarily stored at 4 °C, and then transferred to a – 80 °C ultra-low temperature freezer for long-term storage within 4 hours.

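### The only test named for beta diversity fixes neither unit nor permutation scheme and has no visit term: pooled over visits it over-rejects for regimen, and visit by visit it leaves change over time untested.

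*Protocol article*

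**What the plan says.** The aims at the end of the Introduction are to "characterize the temporal changes in vaginal microbiome", with beta diversity listed beside the Simpson index and dominant taxa, and to compare the two regimens on microbiome composition.

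Under Primary outcome: "Measurement time points were established at baseline, and at 1 month, 3 months, 6 months, and 12 months post-treatment". The Abstract and Table 1 give the same five sampling visits.

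Under Diversity analysis and community structure assessment: "Beta diversity was assessed by calculating Bray-Curtis distances and weighted/unweighted UniFrac distances between samples". The one inferential method that follows is PERMANOVA with adonis, which "was used to quantitatively evaluate the variation in microbial community structure explained by clinical grouping". That section mentions no visit, no woman identifier and no restriction on permutations.

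Under Statistical analysis, repeated visits are handled by linear mixed models for continuous clinical outcomes and by "generalized linear mixed models (GLMM) for microbiome features (e.g., relative abundance of key taxa"), with group, time and their interaction as fixed effects.

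**The concern.** Swabs from the same woman resemble each other, and her regimen does not change between visits. Unless it is given a permutation design, adonis shuffles rows freely. If the rows are all swabs from all visits, the shuffling hands one woman's swabs to both regimens, which cannot happen in the data. The reference distribution is then too narrow, and the regimen p-value too small.

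If the rows are the swabs of a single visit, this problem does not arise. But no such analysis tests whether community structure changes under therapy, or whether it changes differently by regimen. Those are the questions that aims 1 and 2 put to the beta-diversity data. At stake is either a spurious claim that the two regimens shape the vaginal community differently, or a longitudinal aim with no test behind it.

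**Working it through.** **The plan's own figure.** The article gives no sample size, power or error rate for beta diversity. Its sample size calculation concerns the Simpson index, so there is no stated figure to reproduce here.

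**Inputs from the article.**
- Women: "target sample size of 110 participants (55 participants per group").
- Swabs: "Vaginal swabs collected at baseline and 1, 3, 6, 12 months undergo 16S rRNA sequencing", which is 5 per woman and up to 110 × 5 = 550 in all.
- Level: "All tests will be two-sided, with a significance level of *α* = 0.05".
- Distance: Bray-Curtis, one of the distances named.

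**Input not in the article.** The correlation ρ between swabs of the same woman is assumed to lie between 0.1 and 0.7.

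**Rough check in one dimension.** For a mean compared between groups fixed by woman, treating 5 swabs as independent understates the variance by 1 + (5 − 1)ρ. The true two-sided error is then P(|Z| > 1.96/√(1 + 4ρ)):
- ρ = 0.1: 1.96/√1.4 = 1.66, error 9.8%
- ρ = 0.3: 1.96/√2.2 = 1.32, error 18.6%
- ρ = 0.5: 1.96/√3.0 = 1.13, error 25.8%
- ρ = 0.7: 1.96/√3.8 = 1.01, error 31.5%

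PERMANOVA adds the same excess over many taxa, so rates at or above these are expected.

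**Simulation, no regimen effect.** Two separately written simulations used 55 + 55 women, 5 swabs each, Bray-Curtis distances and 199 permutations. The first used 12-taxon logistic-normal communities (300 runs per setting). The second used log-normal compositions with 5 or 20 taxa (600 runs per setting). False rejection of the regimen null at nominal 5%, all swabs pooled and freely permuted:

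| ρ | 12 taxa | 5 taxa | 20 taxa |
|---|---|---|---|
| 0.1 | 13% | 11% | 10.5% |
| 0.3 | 33% | 18% | 31.5% |
| 0.5 | 49% | 29% | 58.5% |
| 0.7 | 69% | 41% | 76.7% |

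- *Whole women permuted instead:* 4% to 6% (12 taxa) and 3.5% to 6.7% (5 and 20 taxa).
- *A different community model:* with three community types and visit-to-visit persistence of 0.3, 0.5, 0.7 and 0.85, free permutation gives 13%, 24%, 39% and 48%. Whole-woman permutation gives 3% to 7%.
- *Cause isolated:* with no persistence, or ρ = 0, free permutation gives 4.7% and 5.5%. Within-woman correlation is what drives the excess.
- *One visit only:* 3% to 4.5% for ρ from 0.3 to 0.9 (200 runs each). The level holds, but the analysis contains no visit effect and no regimen-by-visit effect.

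**Does another stated method fill the gap?** The linear mixed models take clinical scores. The generalized models take features such as one taxon's relative abundance. The repeated-measures ANOVA and the generalized estimating equations named in the Abstract are also methods for a single response. None of them takes a distance matrix.

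**The case against.** The article never says that visits are pooled. Distances between samples exist equally in a visit-by-visit analysis, and permutation blocks are the kind of detail that a full protocol or analysis plan may settle. This stands: the inflation is conditional on pooling and is not a fact of the plan. It does not dispose of the point, because the article names the test, the function and the factor, and that combination does not meet its own longitudinal aim under either reading.

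Two stronger readings are tempting and are not supported.

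- A reader might infer that the plan cannot see change over time. The plan proposes no freely permuted time term, so the loss of power of such a term is not a property of the plan. Nor is the loss general. With a 0.6 SD drop in the dominant taxon, free permutation still detected change in 96%, 90% and 91% of runs at ρ = 0.3, 0.5 and 0.7. The firm statement is that no test of change is named.
- A reader might infer that a visit-by-visit regimen comparison is simply unadjusted. Cohort classification makes inverse probability weighting the primary balancing approach, and Statistical analysis adds propensity score matching when imbalance is found. Whether either reaches the PERMANOVA is not stated, so the absence of adjustment cannot be assumed.

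The stakes also have a limit. The Abstract names the Simpson index and Lactobacillus abundance as primary outcomes. Beta diversity is part of the stated aims but is not named there.

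**Conclusion.** The point holds in conditional form. The section fixes neither the unit of analysis nor the permutation scheme, and it has no visit term.

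- **Pooled with default permutation:** the regimen test is anti-conservative, with about 10% to 77% false rejection at nominal 5%. The range rests on an assumed within-woman correlation of 0.1 to 0.7 and on the community model. At ρ = 0.5 alone it runs from 29% (5 taxa) to 58.5% (20 taxa). Even ρ = 0.1 roughly doubles the nominal rate.
- **Visit by visit:** the error rate is about 5% when the groups are comparable, but the beta-diversity part of aim 1 and the regimen difference in change have no stated test.

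This should be settled before analysis. It does not show that the trial will report a false regimen difference.

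**What to change.** Under Diversity analysis and community structure assessment, specify a repeated-measures PERMANOVA (adonis2 with an explicit permutation design):

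1. **Regimen:** permute regimen labels across whole women, keeping each woman's swabs together. Setting the woman as the stratum does not serve here, because shuffling within a woman never changes her regimen.
2. **Visit:** permute visits within each woman.
3. **Regimen-by-visit, baseline swabs included:** make this the regimen comparison of change, with regimen labels permuted between women. This term was not simulated for this review.
4. **Confounding:** state that the baseline confounders or propensity score used in the other regimen models apply here too.

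The cost is a change of wording and a few lines of R, with no new data, visits or participants. The downside is that regimen p-values will be less favourable than under free permutation.
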